8	10	Bring both index fingers to each other, repeat until time expires.
9	20	Let participant's both index fingers tap his/her nose. Repetitively with the right (10 s), then with left index (10 s).
10	20	Entrainment. While holding the arms extended, have the participant stamp with his/her right foot according to the stamp frequency of the examiner. Then have him/her repeat with the left foot.

The software development for smartwatch-based and smartphone-based data capture is already finished. Tablet-based data capture will be included as soon as development and tests are completed. The first 3 months of the study consist of a setting up and testing phase, regardless of the tablet-based component. Only then, patients will be recruited and data capture commences and endures for 21 months. Based on a database report of the local EMR system, we expect 120 patients with ET and 954 patients with PD at our local site. A fixed number of follow up visits is not planned during this study. However, patients that will re-appear at the local site according to the usual treatment plan will be identified as follow-up patients to enable data analysis on disease progression.

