**Figure 3 F3:**
[figure not shown]
Overview screen **(left)**: the full examination takes approximately 20-min and starts with questionnaires and heart frequency measurement by the smartwatch. Before hand-tremor assessment starts, smart-watch calibration is required. Questionnaire screen **(upper right)**: showing one item of the PD-NMS instrument. Initial signal processing on the smartphone **(bottom right)**: visualization of average amplitude and frequency, raw acceleration data during examination section 3 and frequency spectrum. The acceleration data illustrates a simulated case of re-emergent tremor on the time axis. FFT, Fast Fourier Transform. Data capture and analyses of tablet-based spiral drawing is not implemented yet.

Data captured by spiral drawing will be processed for angular feature detection, direction inversion and pattern deviation from ideal spiral according to Zham et al. (8). The sum of all captured and processed data will train a neural network model to predict the diagnosis label (PD, ET, none of them) and identify data patterns that could represent new biomarkers. The model will be trained applying Google Tensor Flow-based Network architectures using Convolutional neural networks (CNN) as they have shown highly promising pattern recognition results in medical images (11). In addition, long short-term memories (LSTM) networks will enable time-series analysis to account for temporal dynamics within the protocol-based examination and tablet-based spiral drawing. Both core methods (CNN + LSTM) will continuously be evaluated separately and in combination (e.g., using LSTM on top of CNN-extracted features). Sensitivity, positive predictive value/precision and accuracy will be calculated based on existent diagnosis labels using nested cross-validation. Statistical significance of classification results will be calculated by permutation tests. Univariate and Multivariate Analyses will be performed based on standard statistical regression analyses (e.g., logistic regression). This is necessary, first, to continuously and critically compare performance of Deep Learning black boxes with classical statistical approaches and second, to get a deeper understanding of the inter-related input features and their predictive power to classification results.

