A concrete formulation of hypotheses is limited since we did not find any similar systems that were evaluated in studies from which we can derive a reliable patient sample size calculation based on statistical power analyses. Therefore, following key performance indicators (KPI) are aimed at the end of the study period based on classification performances in other disease domains (11, 20):
- **KPI 1:** >80% of all recruited participant cases will provide complete data as described in data capture Table S1 in the pseudonymized research database.- **KPI 2:** >90% accuracy, >90% sensitivity, >90% positive predictive value for classifying ET and PD by the tested model using nested cross validation.

All data items from smartwatch-based data and questionnaires that are relevant for data analysis are specified in the standardized Operational Data Model by the clinical data interchange standards consortium and will be available on the MDM-Portal.

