### Limitations

A proper sample size calculation was not performed, since it cannot be inferred how many samples the model will require to approach the targeted key performance indicators as—to our knowledge—there was no similar model trained and tested within this domain. However, there are basic assumptions of machine learning principles, stating that the size of training samples should be a multiple of the number input variables and output classes of the model to perform reasonably well (21). The smart-watch-based examination is the most data-consuming procedure capturing acceleration (A) and rotation (R) in 3 axes in 10 different examination sections at 2 different hands. This results in approximately 2 (A+R)^*^ 3 ^*^ 10 ^*^ 2 = 120 input variables. Three output classes are modeled (PD, ET, control: none of them or healthy). Ideally, we require a multiple of 120 ^*^ 3 training samples. Based on the EMR report, we can expect at least 500 patients with PD or ET at our local site, if every second will provide consent. Additionally, most of the patients will attend the ambulance with their spouses or partners, who will also be asked to participate as controls. We are convinced that the required recruitment number is approachable within the study phase, since the data capture is non-obtrusive without any interventional character.

In the case of reaching the targeted key performance indicators, they should still be taken with caution. The predictive capability will never be 100% flawless. This is even more likely to be the case if the system is tested in different environments with different examiners. The study will acquire at least two different regular examiners to train robustness for inter-examiner differences. We believe that this work has established a straight forward and fully-documented examination framework, that can be reproduced in other environments. After study completion, the resulting model, implementation code and execution description will be published as open source and supplied with anonymized training data samples.

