## Interpretation of Anticipated Results

### Results

Each of the three technology-driven data capture settings is expected to show high potential to classify tremor-related diseases. Synchronization of these multimodal data and integrative pattern recognition analyses are expected to provide deeper insights into tremor characteristics. All of the technical devices used within this study have recently evolved to affordable mass products. Coupled with highly customizable apps, some of these devices already received FDA approval as for instance the Kardiaband app by AliveCor, the first FDA-cleared smartwatch-based ECG reader (22). This demonstrates the qualified use of such smart wearables not only for fitness or wellness purposes but also for valid medical use. A further advantage of the SDS system—compared to commercial and proprietary systems as the KinetiGraph™ system—is that all of its devices can be programmed and adapted by any Apple-based App developer through well-established Software Development kits and therefore preventing vendor lock-in. Once our system has reached the required level of accuracy, sensitivity and precision, regulatory steps will be taken for medical device approval and rollout to further sites. As a consequence, the system will not replace but could decisively extend diagnostic processes, which are currently suffering from high misdiagnoses rates in this domain (2, 3).

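### KPI 2 sets 90% targets without a class rule; at the expected 8:1 PD:ET mix, some readings it leaves open let it be met while most ET patients are missed

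*Protocol article*

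**What the plan says.** All references are to the protocol article.

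- Methods and Anticipated Results, KPI 2: the target is ">90% accuracy, >90% sensitivity, >90% positive predictive value for classifying ET and PD by the tested model using nested cross validation".
- The same section names the metrics: "Sensitivity, positive predictive value/precision and accuracy will be calculated based on existent diagnosis labels using nested cross-validation". It adds: "Statistical significance of classification results will be calculated by permutation tests". The permutation statistic is not given.
- Materials and Equipment: "we expect 120 patients with ET and 954 patients with PD at our local site".
- Limitations: "we can expect at least 500 patients with PD or ET at our local site, if every second will provide consent". The same section models three output classes: PD, ET and control. The number of controls is not stated.
- Interpretation of Anticipated Results, Results: "Once our system has reached the required level of accuracy, sensitivity and precision, regulatory steps will be taken for medical device approval".

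The article gives no positive class, no per-class requirement and no averaging rule for KPI 2.

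**The concern.** Sensitivity and PPV are undefined until a positive class or an averaging rule is named, and pooled accuracy depends on the class mix. With about eight PD patients for each ET patient, the larger class dominates any pooled or prevalence-weighted figure. The same confusion matrix can then pass KPI 2 on one reading and fail it on another, and the choice could be made after the results are known.

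This matters for two reasons. The article offers the KPIs in place of formal hypotheses and a power-based sample size. It also links reaching the required performance to regulatory steps. Telling ET from PD is the clinical question, and ET is the class that the ambiguity leaves exposed.

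**Working it through.** **Inputs.** 954 PD and 120 ET (Materials and Equipment); one in two consenting (Limitations); thresholds of 90% for three metrics (KPI 2). Assumptions: consent is equal in both diseases; where controls enter, their number is varied because the article gives none.

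**The plan's own figure.** (954 + 120) × 0.5 = 537, consistent with the stated lower bound of 500. Equal consent gives 477 PD and 60 ET. The PD share is 954/1074 = 88.8%.

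**Benchmark, PD and ET patients only.** Calling everyone PD gives accuracy 477/537 = 88.8%, PD sensitivity 100% and PD PPV 477/537 = 88.8%. That is just short of the target with no discrimination at all.

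**PD as positive class.** Let all PD be correct and k ET be found, the rest being called PD.

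- Accuracy = (477 + k)/537; PD PPV = 477/(537 − k).
- k = 8: accuracy 485/537 = 90.3%, PD sensitivity 100%, PD PPV 477/529 = 90.2%. All three pass.
- k = 7: PD PPV = 477/530 = 90.0% exactly, which is not above 90%. So 52 missed ET is the maximum.
- At k = 8, ET sensitivity is 8/60 = 13.3% and balanced accuracy is (1 + 8/60)/2 = 56.7%.

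**Prevalence-weighted averages, same model.** Sensitivity = 485/537 = 90.3%; PPV = (477 × 0.9017 + 60 × 1)/537 = 91.3%. Both pass.

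**Per-class or macro-averaged reading, same model.** ET sensitivity is 13.3% and macro-averaged sensitivity 56.7%. Both fail. To exceed 90% in ET, 55 of 60 must be found.

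**Allowing PD errors (PD called ET).** Accuracy above 90% permits at most 53 errors in total, since 0.1 × 537 = 53.7.

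| PD errors | Most ET that can be missed |
|---|---|
| 0 | 52 (PPV is the limit) |
| 10 | 43 |
| 20 | 33 |
| 40 | 13 |

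**Other recruitment totals, no PD errors.** With 954:120, 105 of 120 ET can be missed. With 444:56 (500 patients), it is 49 of 56.

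**Adding controls.** Correctly classified controls raise pooled accuracy and leave PD PPV unchanged, so 52 ET called PD still passes. With 100 correct controls and every ET called control, accuracy is (477 + 100)/637 = 90.6%, and PD sensitivity and PD PPV are both 100%. KPI 2 is then met for PD with no ET found. More correct controls only raise the accuracy.

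**Permutation test.** Take accuracy as the statistic and the predictions as fixed (both assumptions). The chance that all eight ET calls are right under shuffled labels is C(60,8)/C(537,8) = 1.6 × 10⁻⁸. In 20,000 simulated permutations the highest accuracy was 89.2%, against 90.3% observed. The model that misses 52 of 60 ET is therefore highly significant.

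**The PPV threshold read for ET.** With 55 ET found, 55/(55 + FP) > 0.9 allows at most 6 false positives. If all come from PD, specificity among PD must be at least 471/477 = 98.7%. A model that is 90% correct in both diseases has ET PPV of 54/(54 + 47.7) = 53%.

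**The case against.** The strongest reply is that KPI 2 speaks of classifying both ET and PD, so its thresholds may be meant for each disease. On that reading the 8-of-60 model fails outright, and nothing in the article names PD as the sole positive class. This stands. A reader might infer that KPI 2 as written simply admits a model that ignores ET. The text supports only that it may, depending on a rule it does not state.

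Other limits also stand:

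- Fifty-two is a maximum that needs every PD patient to be right. The allowance shrinks quickly as PD errors accumulate.
- A reader might infer that calling everyone PD nearly meets the target. That holds only within PD and ET patients. With, say, 537 controls, always-PD accuracy is 477/1074 = 44.4%.
- With 537 correct controls and no ET found, accuracy is 1014/1074 = 94.4%, but that alone does not meet KPI 2. If all 60 ET are called PD, PD PPV is 88.8% and fails. At least 8 of them must be called control for it to pass.
- The article never presents the permutation test as a test of the 90% target. The point is only that it does not close the gap.
- The study is exploratory, Limitations asks for caution even if the KPIs are reached, and the regulatory sentence states an intention, not an automatic step.

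It can also be said that a condensed article leaves averaging rules and intervals to a fuller document. That is fair for intervals and for the permutation statistic, and it means one cannot say that other metrics are absent from the study's plans. It is weaker for the criterion itself, which the article publishes with its metrics and thresholds. The caution in Limitations concerns imperfect prediction and transfer to other settings, not class mix. Stepwise Procedures also leaves the analysis open to refinement after data are collected, so the choice of reading is not protected.

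**Conclusion.** The point holds as a badly fixed success criterion. KPI 2 gives opposite verdicts on the same results according to a class rule that the article does not state. With PD as the positive class or prevalence weighting, it can be met with up to 52 of 60 ET missed and balanced accuracy as low as 57%. About 33 can be missed with 20 PD errors and 13 with 40. With 100 or more correctly classified controls, it can be met for PD with every ET called control. On a per-class reading these models fail.

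The counts rest on the article's site figures and 50% consent, with equal consent in the two diseases assumed. The arithmetic is exact given those inputs. What is uncertain is which reading the investigators intend.

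**What to change.** Restate KPI 2 by class before the results are seen:

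1. Require sensitivity above 90% in PD and in ET separately. State it as per-class sensitivity; sensitivity in one disease equals specificity for the other only when there are two classes.
2. Make balanced accuracy, the mean of the per-class sensitivities, the headline figure in place of pooled accuracy.
3. Report PPV for each class at the stated clinic mix, with 95% confidence intervals. Note beside it that ET PPV above 90% would need about 98.7% specificity among PD patients.
4. Next to any pooled accuracy, print the majority-class benchmark for the population it is computed on: 88.8% for PD and ET only, recomputed when controls are included.
5. Describe the permutation test as a check against chance only.

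If a fuller document already contains a class rule, state it with KPI 2. No new data are needed: the cost is a reworded target and a few lines of analysis code. The downside is that the headline figure may look less favourable.

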### Limitations

A proper sample size calculation was not performed, since it cannot be inferred how many samples the model will require to approach the targeted key performance indicators as—to our knowledge—there was no similar model trained and tested within this domain. However, there are basic assumptions of machine learning principles, stating that the size of training samples should be a multiple of the number input variables and output classes of the model to perform reasonably well (21). The smart-watch-based examination is the most data-consuming procedure capturing acceleration (A) and rotation (R) in 3 axes in 10 different examination sections at 2 different hands. This results in approximately 2 (A+R)^*^ 3 ^*^ 10 ^*^ 2 = 120 input variables. Three output classes are modeled (PD, ET, control: none of them or healthy). Ideally, we require a multiple of 120 ^*^ 3 training samples. Based on the EMR report, we can expect at least 500 patients with PD or ET at our local site, if every second will provide consent. Additionally, most of the patients will attend the ambulance with their spouses or partners, who will also be asked to participate as controls. We are convinced that the required recruitment number is approachable within the study phase, since the data capture is non-obtrusive without any interventional character.

In the case of reaching the targeted key performance indicators, they should still be taken with caution. The predictive capability will never be 100% flawless. This is even more likely to be the case if the system is tested in different environments with different examiners. The study will acquire at least two different regular examiners to train robustness for inter-examiner differences. We believe that this work has established a straight forward and fully-documented examination framework, that can be reproduced in other environments. After study completion, the resulting model, implementation code and execution description will be published as open source and supplied with anonymized training data samples.

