- First, there is poor integration of clinically relevant motor and non-motor phenomena. Especially, changes in tremor characteristics in relation to provoking circumstances (e.g., specific motor or cognitive actions) are currently not integrated into electronic tremor analyses. The SDS system utilizes different monitoring settings in one easy-to-follow examination at a health care facility: (A) Movement monitoring using two smartwatches at both patient wrists in a pre-defined neurological examination that provokes different tremor types. (B) Electronic questionnaires regarding medication/drug consumption, family history and non-motor symptoms on a smartphone. (C) Archimedean Spirals drawn by the patient on a tablet. Each of these three settings viewed individually already show high potential to classify or stratify tremor-related diseases (7–9). However, synchronization of these multimodal data (A–C) and advanced pattern recognition analyses such as Deep Learning would unlock a new integrative approach to boost classification performance and to find new phenotypical characteristics. In particular, Deep Learning methods have recently shown high classification performance in pattern recognition in other medical domains if a large amount of expert-tagged training data is available (10, 11).- Second, there is a lack of open data repositories and data standards to share best practices of existing smart wearable solutions. This project uses the Medical-Data-Models Portal (MDM Portal) that has evolved to the largest European information infrastructure for medical data models (12). This portal will be used to harmonize and enrich developed data models toward established data standards and foster interoperability with other health information systems. Moreover, active collaboration with the Neurology Department and Task Force on Technology will align clinical and technical key requirements with current ongoing developments.

A 2-year prospective exploratory study is going to be conducted in which the SDS system will be applied within a 20-min data capture session for each included participant. The objective is to train a Deep Neural Network that is capable of predicting the disease entity (PD, ET, none of them) and to identify new phenotypical characteristics based on the fully integrated and pseudonymized study data.

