## Materials and Equipment

The project is planned as a 2-year prospective exploratory study at the Movement Disorders outpatient clinic at the University Hospital Münster. Each patient diagnosed with PD (ICD 10-GM: G20.-) or ET (ICD-10-GM G25.0) and visiting the outpatient clinic is going to be a potential study participant. To be included, each patient must receive, fully understand and sign the informed consent form. All requirements of the updated EU data protection regulation from the start of May 2018 will be strictly adhered to. The study design is registered on Clinicaltrial.gov (Identifier: NCT03638479).

Figure 1 provides an overview of the SDS system and its intended processing steps. Three Apple-based mobile devices will be customized for different monitoring settings. Smartwatch-based examination takes 10-min including calibration and putting them on both wrists. The total assessment time including questionnaires (8 min), drawing one spiral (1–2 min) is 20 min.

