### Recruitment

Each patients and his/her accompanying person (e.g., life partner), who visit the movement disorders outpatient clinic at the University Hospital in Münster and fulfill the aforementioned criteria will be asked to participate in the study. In most cases, each patient will be accompanied by a familiar person. These companions represent age-matched healthy controls. Each participant will be informed about the SDS system, the data to be captured, pseudonymized, transferred and stored for data analysis. Study inclusion starts once informed consent form has been signed.

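### The third class holds only companions, so 'none of them' cannot be evaluated in patients with another tremor, and no stated step makes the companions age-matched or healthy

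*Protocol article*

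**What the plan says.** The Introduction states the aim as a network "capable of predicting the disease entity (PD, ET, none of them"), and Methods and Anticipated Results repeats these three labels. Limitations describes the third class differently: "Three output classes are modeled (PD, ET, control: none of them or healthy").

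Patient eligibility, in Materials and Equipment, is "Each patient diagnosed with PD (ICD 10-GM: G20.-) or ET (ICD-10-GM G25.0) and visiting the outpatient clinic is going to be a potential study participant". The only other participants are accompanying persons. Recruitment says of them: "These companions represent age-matched healthy controls". Limitations adds that "most of the patients will attend the ambulance with their spouses or partners, who will also be asked to participate as controls". Recruitment asks patients and companions to meet criteria given earlier, and closes with "Study inclusion starts once informed consent form has been signed".

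KPI 2 (Methods and Anticipated Results) asks for more than 90% accuracy, sensitivity and positive predictive value, and is worded for the classification of ET and PD. The Results part of Interpretation of Anticipated Results says that reaching the required performance leads to medical device approval steps, rollout to further sites and an extension of diagnostic processes.

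**The concern.** Not having PD or ET and being healthy are different states. A patient with tremor from another cause is in the first group but not the second. Such patients are the hard part of a differential diagnosis, and Future Work acknowledges that other causes of tremor exist. If the third class contains only companions, good performance on it shows that the system can tell patients from people who came with them. It says nothing about a patient with a third kind of tremor.

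The description of the companions raises a second issue. If they differ from patients in age or sex, part of the patient-versus-companion separation could reflect those differences and then be read as a movement biomarker.

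Third, the companions can enter the denominator of an accuracy target. A large and fairly easy class can lift overall accuracy while ET, the smaller patient group, is missed.

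**Working it through.** **1. Who can be in each class.** Setting the sections side by side:

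- PD and ET: patients with the corresponding diagnosis code (Materials and Equipment).
- Third class: companions only (Recruitment; Limitations).
- Patients whose tremor is neither PD nor ET: none eligible under the stated rule.

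The cross-validated results for the third class therefore describe companions and nobody else.

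**2. What makes companions age-matched and healthy.** The earlier criteria that Recruitment points to are a PD or ET diagnosis and signed consent. The diagnosis criterion cannot apply to a control, which leaves consent. Partners may be close in age, but closeness is not matching, and pairing partners does not balance sex. If a share *m* of patients is male and every companion is an opposite-sex partner (assumption), the male share among companions is 1 − *m* and the imbalance is *m* − (1 − *m*) = 2*m* − 1. This is zero at *m* = 0.5. The article gives neither *m* nor any age figure, so the size of confounding cannot be computed.

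**3. The article's own numbers.** Materials and Equipment expects 954 PD and 120 ET patients, 1,074 in all. Limitations assumes that every second patient consents: 1,074 × 0.5 = 537, which agrees with its floor of at least 500. Applying 50% to both groups gives 477 PD and 60 ET.

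**4. KPI 2 accuracy with and without companions.** Take a model that calls every patient PD.

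- Patients only: 477 / 537 = 88.8%, below the target.
- Three classes, with *c* companions all classified correctly: (477 + *c*) / (537 + *c*).
- This exceeds 0.90 when 477 + *c* > 483.3 + 0.9*c*, that is 0.1*c* > 6.3, so *c* > 63.
- 63 / 537 = 11.7%, so fewer than one patient in eight would need to bring a companion who takes part.

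The number of companions is not given. Assuming that 25% to 100% of the 537 patients bring one who takes part:

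| Companions | Three-class accuracy | ET cases found |
|---|---|---|
| 134 | 611 / 671 = 91.1% | 0 of 60 |
| 537 | 1,014 / 1,074 = 94.4% | 0 of 60 |

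**5. Would the other two targets catch this?** Computed per class, yes: ET sensitivity is 0 / 60 = 0%, and PD positive predictive value is 477 / 537 = 88.8%. Pooled over classes, no: pooled sensitivity and pooled positive predictive value each equal the accuracy. The article does not say which is meant.

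**The case against.** The study is exploratory, returns no result to patients, asks that its indicators be read with caution, and says the system will not replace existing diagnostic processes. KPI 2 is already worded for ET and PD, and that contrast does not depend on companions. The article is a condensed account: companion criteria and demographic items may be in the full protocol or in Table S1, neither of which is shown. Most companions are expected to be partners, who are usually similar in age and not blood relatives.

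Much of this stands, and it rules out several stronger readings that a reader might infer:

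- *That the three-way classification is untestable.* It is not. PD versus ET versus companion can be trained and cross-validated as planned. Only the reading of 'none of them' as another tremor diagnosis lacks data.
- *That accuracy in practice has a calculable ceiling.* That would need the share of other tremors in the intended-use population, which the article does not give. It would also need all those patients to be assigned to PD or ET, although the model has a third output.
- *That sex or age demonstrably confounds the control contrast.* No figure supports this, and the effect may be zero.
- *That companions are unscreened, or that their age and sex go unrecorded.* This would be inferred from silence in a condensed article.

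What remains rests on what the article does say: two unlike meanings for one class, eligibility that supplies only one of them, an age-matching claim that recruiting companions does not deliver, and a reference to criteria that cannot apply to controls. The KPI 2 wording leaves open whether accuracy is taken over patients or over all three modelled classes.

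**Conclusion.** The point holds as a matter of class definition and scope of claim. The design supports conclusions about PD versus ET versus companions. It does not support a conclusion about 'none of them' in patients with tremor of another cause, and the diagnostic-support statement should not reach them. The description of companions as age-matched and healthy is not backed by a stated step; its consequence for bias is unknown in size and possibly nil.

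The one effect that can be sized concerns KPI 2. A model that detects no ET case scores 88.8% accuracy in patients, yet passes 90% across three classes once more than 63 companions are included. This assumes equal 50% consent in both patient groups and that every companion is classified correctly. Sensitivity and positive predictive value targets may still catch such a model, depending on how they are averaged. The ET-versus-PD comparison itself is unaffected by who the controls are.

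**What to change.** - Name the third class 'companion controls' throughout, and limit the objective and conclusions to PD versus ET versus companions. State that performance in patients with other tremor diagnoses is not evaluated.
- State that KPI 2 accuracy, sensitivity and positive predictive value are computed on PD and ET patients only.
- Drop the claim of age-matching, and give companions their own entry criterion: no known tremor or neurological diagnosis.
- Adjust or weight the patient-versus-companion contrast for age and sex, and report beside it a benchmark that uses age and sex alone.

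The cost is some rewording, slightly more analysis, the exclusion of a few companions and a narrower claim. If age and sex are already among the data items in Table S1, no new data capture is needed for the adjustment. Admitting patients with other tremor diagnoses would give 'none of them' its diagnostic meaning, but that is an optional extension and not part of this fix.
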